# 3D-printed individualized tooth-borne tissue retraction devices compared to conventional dental splints for head and neck cancer radiotherapy: a randomized controlled trial

**DOI:** 10.1186/s13014-021-01803-8

**Published:** 2021-04-17

**Keywords:** Intensity-modulated radiotherapy, Particle therapy, Toxicity, Radiation-induced oral mucositis, Xerostomia, Squamous cell carcinoma, Salivary gland tumor

## Abstract

**Background:**

Despite modern treatment techniques, radiotherapy (RT) in patients with head and neck cancer (HNC) may be associated with high rates of acute and late treatment-related toxicity. The most effective approach to reduce sequelae after RT is to avoid as best as possible healthy tissues and organs at risk from the radiation target volume. Even small geometric changes can lead to a significant dose reduction in normal tissue and better treatment tolerability. The major objective of the current study is to investigate 3D printed, tooth-borne tissue retraction devices (TRDs) compared to conventional dental splints for head and neck RT.

**Methods:**

In the current two-arm randomized controlled phase II trial, a maximum of 34 patients with HNC will be enrolled. Patients will receive either TRDs or conventional dental splints (randomization ratio 1:1) for the RT. The definition of the target volume, modality, total dose, fractionation, and imaging guidance is not study-specific. The primary endpoint of the study is the rate of acute radiation-induced oral mucositis after RT. The quality of life, local control and overall survival 12 months after RT are the secondary endpoints. Also, patient-reported outcomes and dental status, as well as RT plan comparisons and robustness analyzes, will be assessed as exploratory endpoints. Finally, mesenchymal stem cells, derived from the patients’ gingiva, will be tested in vitro for regenerative and radioprotective properties.

**Discussion:**

The preliminary clinical application of TRD showed a high potential for reducing acute and late toxicity of RT in patients with HNC. The current randomized study is the first to prospectively investigate the clinical tolerability and efficacy of TRDs for radiation treatment of head and neck tumors.

*Trial registration*: ClinicalTrials.gov; NCT04454697; July 1^st^ 2020; https://clinicaltrials.gov/ct2/show/record/NCT04454697.

## Background

Despite modern radiation techniques, e.g. intensity-modulated radiotherapy (IMRT), radiation treatment may be associated with high rates of severe treatment-related toxicity [1, 2]. Higher grade radiation-induced oral mucositis (RIOM) (≥ Common Terminology Criterion [CTC] grade III), common dose-limiting toxicity, occurs in up to 60% of patients [3–5]. The rate of RIOM is further increased by the application of simultaneous systemic therapies (e.g., chemotherapy). The immediate consequences of this are limited tolerability of therapy and reduced compliance, and an interruption or even discontiuation of treatment [6]. If epitheliolysis and ulcerations occur, the risk of bacterial superinfection with possible complications, including sepsis, increases. In the long term, mucositis causes dry mouth, taste disorders, pain, and difficulty swallowing, and weight loss, which increases the frequency of hospitalization. Many prospective clinical studies demonstrated a reduction in the quality of life in this context [7, 8].

The probability of radiogenic damage to epithelial cells is dose-dependent [9]. Established risk factors for the development of oral mucositis during radiotherapy (RT) include decreased oral hygiene and smoking. So far, many approaches have been postulated for the prevention and treatment of mucositis, but there are no clear recommendations other than adequate care and analgesia. A total of 320 studies listed about oral mucositis at "http://www.clinicaltrials.gov" underscore the clinical relevance of the topic.

However, the most effective approach to reducing acute toxicity after RT is to avoid as best as possible healthy tissues and organs at risk from the high-dose area of the radiation field. Isolated case reports [10] and several retrospective studies [11–13] on customized TRDs for RT of head and neck tumors reported reduced rates of mucositis with good tolerability. Currently, there are no prospective studies available.

Usually, there is a close positional relationship in the head and neck area between the gross tumor volume and the adjacent normal tissue and organs at risk. Due to anatomical reasons, including parts of the tongue, jaw, or oral mucosa in the high-dose RT area is often unavoidable. Using TRDs can increase the distance between the tumor and normal tissue in certain areas. Even the smallest geometric change of a few millimeters can significantly reduce the dose of normal tissue with significant benefits for the patient [14]. This is essential in particular for high precision RT, e.g. by IMRT, MRI-guided RT, or heavy ion therapy. Another factor of uncertainty is the mobility of the tongue and the base of the tongue because there is usually no fixation during RT. Proper immobilization can reduce unwanted movements and allow for more precise therapy. Besides increasing the distance between the tumor and healthy tissue to reduce RIOM, TRDs could also be advantageous for precise repositioning of the patient.

Traditionally, manufacturing TRDs that target healthy tissue displacement, tongue immobilization, and precise patient repositioning is complex and time-consuming [15]. This could be the reason conventional dental splints, made of thermoplastic resin, are used as the standard of clinical treatment in many institutions. Therefore, these thermoplastic dental splints will be used in the control arm of the present study. Introducing novel computer-assisted design and manufacturing techniques, e.g. 3D printing, has the potential to simplify TRD's workflow while reducing costs and increasing the quality of TRD. For certain indications, e.g. craniomandibular disorders, the production of aligners and TRDs using the 3D printing process is already established in our institution [16, 17]. The materials and methods used are approved and tested for intraoral use. The 3D printing process enables economical and flexible production.

The current trial aims to evaluate TRDs for individualized and effective RT of patients with malignant HNC to protect normal tissue and improve treatment tolerability. At the cellular level, the high regenerative potential of mesenchymal stem cells (MSCs) has been characterized in detail [18]. They can be isolated from various tissues such as bone marrow and adipose tissue, but also the head and neck region (including the gingiva). The importance of gingival MSCs for radioprotection in the head and neck area has not been elucidated.

## Methods/design

The current single-center, two-arm, randomized controlled phase II trial anticipates an enrollment of a maximum of 34 patients who meet the inclusion criteria. Patients will receive 3D printed dental TRDs or conventional dental splints (in a randomization ratio of 1:1 via block randomization using an online randomization tool). TRDs are pre-fabricated using 3D printing and are tailored to the individual patient and treatment intention. Each TRD comprises a fixation piece on the tooth which allows the opening of the mouth and the mandibular protrusion, the reproducible positioning, and the covering of the teeth in combination with lip- and cheek spacing. Also, a retraction part allows the displacement of the tongue. An example of a clinical case is shown in Fig. 1. A publication summarizing details of the design process and TRD fabrication is currently under preparation. Conventional dental splints are protective plastic stents covering the teeth to reduce the radiation overdose caused by dental restoration materials. No additional retraction parts or spacing devices are attached.

### Inclusion criteria

The inclusion criteria are: diagnosed malignant tumors in the head and neck region; clinical target volume includes parts of one or several of the following anatomical regions: the upper jaw, the lower jaw, the hard palate, the tongue, the floor of the mouth, the buccal mucosa, the soft palate and the base of the tongue; an indication of adjuvant or definitive RT; age ≥ 18 years; Karnofsky performance score ≥ 60; complete wound healing after the surgical intervention; written informed consent; the ability of the subject to understand the character and individual consequences of the trial; for women of childbearing age (and men), adequate contraception.

### Exclusion criteria

Exclusion criteria are: previous head and neck RT; multifocal diffuse tumor growth; patients who have not recovered from the acute toxicities of previous therapies; trismus (mouth opening ≤ 2 cm); simultaneous chemo/immunotherapy; evidence that the patient cannot adhere to the study protocol (e.g., non-compliance); the refusal of patients to participate in the study.

### Radiation therapy

Radiation treatment will be carried out according to the current standard in our institution, following current clinical guidelines for HNC. The definition of the target volume, modality, total dose, fractionation, and imaging guidance is not study-specific. Simultaneous systemic therapies, particularly chemo- or immunotherapy, are not allowed in the current study. Due to the various histological entities projected for the current trial, a wide range of different treatment approaches is possible.

For treatment planning, patients will be immobilized with an individual immobilization mask. All patients will receive a non-contrast planning CT scan with a layer thickness of 3 mm and, if possible, also a contrast-enhanced CT or magnetic resonance imaging (MRI) for an optimal definition of the target volume. Treatment planning will be carried out using Syngo PT-Planning (Siemens, Erlangen, Germany) and RayStation® (RaySearch Laboratories, Stockholm, Sweden) planning software. Automated multi-atlas-based segmentation of normal tissue and organs at risk, including salivary glands, tongue, hard and soft palate, and mandible, will be performed according to EORTC guidelines using the software RayStation®. Dose constraints for normal tissues and organs will be respected according to the Quantitative Analyses of Normal Tissue Effects in the Clinic (QUANTEC) [20, 21]. According to standard procedures in our clinic, IMRT will be performed 5 fractions per week under image guidance with daily CT images and position correction using volumetric modulated arc therapy. If indicated, particle therapy will be done 5–6 fractions per week with protons or carbon ions. The active raster scanning technology will be used for the application of orthogonal X-ray image guidance and daily position correction. The target volume definition and the dose prescription will be left to the discretion of the treating radiation oncologist, following current clinical guidelines for HNC [22, 23].

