### Study endpoints

The primary endpoint of the study is the rate of acute RIOM after RT with TRD compared to conventional dental splints. To allow an objective evaluation of RIOM complementary to clinical questionnaires, the oral cavity and oropharynx are subdivided into eight anatomical regions (Table 1). Based on previous RIOM studies [3–5], we defined the assumed rate of severe oral mucositis (≥ CTC grade III) as 60% in the treated anatomical region and its direct proximity. The primary target value is to prevent severe RIOM (≥ CTC grade III) in the anatomical regions directly adjacent to the CTV in 75% of patients with TRD. To assess the primary endpoint, all patients receive a diagnostic video endoscopy of the oral cavity and oropharynx performed by an ENT specialist directly after the last radiation treatment. A blinded evaluation of the mucositis grade will be performed.

**Table 1 Tab1:** Anatomical regions of the oral cavity and oropharynx

Oral cavity	Oropharynx
Hard palate	Soft palate/uvula
Buccal mucosa right/left	Oropharyngeal sidewall right/left
Tongue (anterior 2/3)	The base of the tongue
Floor of mouth	Posterior pharyngeal wall

According to the 8th edition of the Union for International Cancer Control (UICC) tumor node metastasis (TNM) classification

Quality of life, local control, and OS 12 months after RT are the secondary endpoints of the trial. After 12 months of study specific follow-up, the patients will continue with regular clinical follow-up examinations. Also, patient-reported outcomes (PRO) and dental status, as well as plan comparisons and robustness analyzes, will be assessed as exploratory endpoints. Also, the functional and differentiation parameters, as well as the regenerative and radioprotective factors of gingival MSCs will be evaluated in vitro.

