#### Power calculation

The trial aims to demonstrate that the rate of oral mucositis in the experimental group, π_E_, is lower than the rate of oral mucositis in the control group, π_C_. Hence, the trial aims to reject the one-sided null hypothesis H_0_: π_E_ ≥ π_C_. We assumed that the rate of oral mucositis in certain anatomical regions in the experimental group will amount to π_E_ = 15%, while the rate of the control group is assumed to be π_E_ = 60%. The assumed rate in the control group is based on published data [4, 5, 27], while the rate in the experimental group reflects the assumption that the experimental intervention can achieve a decrease below grade III for the mucositis in the directly neighboring region of the tumor for 75% of all patients with mucositis. This hypothesis is based on preliminary clinical experience in ten patients treated with TRDs. Under these assumptions, 28 evaluable patients (14 per group) are required to achieve 80% power with a chi-square test at a one-sided 5% level of significance. Assuming a 15% dropout rate, 34 patients (17 per group) will be enrolled. The calculation of the sample size was performed using ADDPLAN v6.1.

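### The regions counted for the primary endpoint are described in three ways, one tied to a CTV probably finalised after allocation on anatomy the TRD has moved; list them per patient before randomisation

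*Protocol article*

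**What the plan says.** The protocol article describes the counted regions in three ways.

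- Study endpoints, control rate: severe mucositis (grade III or worse) is assumed "as 60% in the treated anatomical region and its direct proximity".
- Study endpoints, target value: severe mucositis is to be prevented "in the anatomical regions directly adjacent to the CTV in 75% of patients with TRD".
- Power calculation: the tested quantity is the "rate of oral mucositis in certain anatomical regions in the experimental group", assumed to be 15%. The justification is a decrease below grade III "for the mucositis in the directly neighboring region of the tumor for 75% of all patients with mucositis".

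On the CTV, Radiation therapy states: "The target volume definition and the dose prescription will be left to the discretion of the treating radiation oncologist, following current clinical guidelines for HNC". On the device, Methods/design states: "TRDs are pre-fabricated using 3D printing and are tailored to the individual patient and treatment intention", and adds that "a retraction part allows the displacement of the tongue". Background gives greater separation of tumor and normal tissue as a purpose of the device. The Fig. 1 legend shows a CT and a treatment plan made with the TRD in the mouth.

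On assessment, Study endpoints plans a video endoscopy at the end of radiotherapy and states: "A blinded evaluation of the mucositis grade will be performed". Table 1 lists the anatomical regions. The article gives no list of counted regions fixed per patient before randomisation.

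**The concern.** The three descriptions do not select the same mucosa. The first includes the treated region, the second covers only what borders the CTV, and the third refers to the tumor rather than the CTV. The choice can decide a patient's outcome. The TRD patient in Fig. 1 has grade III mucositis in the high-dose area and an unaffected tongue surface facing it. That patient would most naturally be an event under the first description and a non-event if only the spared neighbor counts.

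The CTV-based description raises a second problem. The device acts on adjacency itself. If adjacency is judged on the final CTV, a tongue surface bordering the CTV in a control patient may not border it in a comparable TRD patient. Severe mucositis there would count in one arm and not in the other. A difference between arms could then partly reflect which regions were counted rather than which mucosa was spared. A blinded grader does not prevent this if the set of regions already depends on the device.

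Eligible CTVs may also lie in the upper or lower jaw, for which Table 1 has no region, so adjacency there needs a rule.

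**Working it through.** **The plan's own figure.** Inputs from Power calculation: 60% vs 15%, one-sided 5%, 80% power, chi-square test, 15% dropout. With mean rate 0.375:

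n per group = [1.645·√(2·0.375·0.625) + 0.842·√(0.60·0.40 + 0.15·0.85)]² / 0.45² = (1.126 + 0.510)² / 0.2025 = 13.2, so 14 per group and 28 in total. Dropout: 14/0.85 = 16.5, so 17 per group and 34 in total. Both stated figures reproduce. Exact power at 14 per group is 82.8%.

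**Which regions those rates describe.** The 15% is 60% × (1 − 0.75). The 60% is stated for the treated region plus its surroundings; the 75% is stated for the neighboring region only. The product therefore combines rates from two sets of regions.

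**Timing.** The article does not say when contouring takes place relative to randomisation. Three statements point to later: the TRD is made for the individual patient; the example plan has it in place; and comparison with a diagnostic CT taken before treatment is foreseen only for selected patients in the experimental arm. Against this, Inclusion criteria requires the CTV to involve named regions, so a rough region-level CTV must be known at screening. Finalisation after allocation is thus a probable inference, not a stated fact.

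**Illustration of size.** The article gives no per-region rates, so everything here is assumed: an event is grade III or worse in any counted region; the control rate is 60%; k regions count in control and k − 1 with TRD; the regions have equal, independent risk q; the TRD has no effect on any mucosa.

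- q solves 1 − (1 − q)^k = 0.60.
- Apparent TRD rate = 1 − (1 − q)^(k−1).
- Rejection probability: exact enumeration of the one-sided 5% chi-square test (pooled variance, no continuity correction).

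| k | q | Apparent TRD rate | Rejects, 14 per group | Rejects, 17 per group |
|---|---|---|---|---|
| 2 | 0.368 | 36.8% | 32.6% | 42.9% |
| 3 | 0.263 | 45.7% | 17.6% | 23.8% |
| 4 | 0.205 | 49.7% | 12.8% | 17.1% |
| equal sets | – | 60% | 4.9% | 5.7% |

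Less extreme assumptions for k = 2, 3, 4 at 14 per group:

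- Only half of TRD patients lose a region (TRD rates 48.4%, 52.9%, 54.9%): 14%, 10%, 8%.
- Within-patient correlation 0.5, beta-binomial (TRD rates 47.5%, 53.6%, 55.8%): 15%, 9%, 7%.
- Perfect correlation: no inflation.

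**If the displaced region also loses risk.** Suppose it keeps one quarter of q. The TRD rate with that region counted is 1 − (1 − q)^(k−1)·(1 − q/4) = 42.6%, 49.3%, 52.3%. With it dropped, the rate is 36.8%, 45.7%, 49.7%. The distortion is 5.8, 3.6 or 2.6 percentage points. With full risk kept it is 60% minus the apparent rate: 23.2, 14.3 or 10.3 points.

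**Sensitivity to one patient.** 8/14 vs 4/14 gives z = 1.53, one-sided p = 0.063. If one TRD patient is reclassified by the choice of regions, 8/14 vs 3/14 gives z = 1.93, p = 0.026.

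**The case against.** The strongest reply is that adjacency can be read as a fixed relation between the named regions of Table 1. The trial's hypothesis makes most sense if the displaced neighbor stays counted, since it is the tissue to be spared, and Fig. 1 shows exactly that surface. On this reading there is no dependence on the device. This is a fair reading, but the target value refers to the CTV and the article does not state a fixed relation. If it is the intended meaning, the text should say so.

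A second reply is that a condensed article leaves operating detail to the full protocol and the SAP. That holds for much detail, but an SAP finalised shortly before database lock cannot create a list made before randomisation.

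A reader might also infer more than the article supports:

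- That discretion over target volume is itself a fault, or that CTVs will be drawn to favor the TRD. The discretion is bounded by clinical guidelines, and nothing suggests biased contouring.
- That the false-positive rate is 33%. This needs two independent regions, every TRD patient losing one, an any-region rule that the article does not state, and displaced mucosa that keeps its full risk. Background argues against the last: it calls epithelial damage dose-dependent and says that a few millimeters matter.
- That the bias favors the TRD. Under an any-region rule, dropping a region can only lower the TRD rate. But mouth opening or protrusion could bring other regions closer, and under an average over counted regions, losing a spared one would hide benefit.

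The one-patient example shows mainly how fragile 28 patients are. It does not show that reclassification will occur.

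**Conclusion.** The point holds in a limited form. The article describes the counted regions in three ways that do not agree, and one of them ties the set to a volume that is probably finalised after allocation, on anatomy the TRD has displaced. Taken literally, the regions at risk of an event may differ by arm, and the stated blinding does not cover their selection. Size and direction cannot be derived from the article. The 13% to 33% rejection rates are upper-end illustrations; 7% to 15% applies with correlation 0.5, and none of the inflation remains with perfect correlation. The change is worth making because it is cheap and protects the 4.9% type I error that applies when both arms are counted alike at 60%. It is not evidence that the trial's result will be biased.

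**What to change.** Before randomisation, record for each patient which Table 1 regions count, using tumor site, pre-treatment imaging and the CTV regions already needed for eligibility. Set one rule on whether treated regions are included and one rule for jaw tumors. Keep the list whatever device is worn and however the final CTV is drawn.

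Define the primary endpoint as grade III or worse in any listed region, and state the 60% and 15% assumptions for that same definition. Have the blinded reader grade all eight regions, and add a sensitivity analysis that counts any of them. Discretion over target volume and dose stays as it is.

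The cost is small. The planned endoscopy already covers the area, so no visit, procedure or patient is added. With the rates kept at 60% and 15%, the 28 evaluable and 34 enrolled stand. The downside is that some lists will not match the final CTV exactly, which may slightly dilute the contrast.

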### Study endpoints

The primary endpoint of the study is the rate of acute RIOM after RT with TRD compared to conventional dental splints. To allow an objective evaluation of RIOM complementary to clinical questionnaires, the oral cavity and oropharynx are subdivided into eight anatomical regions (Table 1). Based on previous RIOM studies [3–5], we defined the assumed rate of severe oral mucositis (≥ CTC grade III) as 60% in the treated anatomical region and its direct proximity. The primary target value is to prevent severe RIOM (≥ CTC grade III) in the anatomical regions directly adjacent to the CTV in 75% of patients with TRD. To assess the primary endpoint, all patients receive a diagnostic video endoscopy of the oral cavity and oropharynx performed by an ENT specialist directly after the last radiation treatment. A blinded evaluation of the mucositis grade will be performed.

**Table 1 Tab1:** Anatomical regions of the oral cavity and oropharynx

Oral cavity	Oropharynx
Hard palate	Soft palate/uvula
Buccal mucosa right/left	Oropharyngeal sidewall right/left
Tongue (anterior 2/3)	The base of the tongue
Floor of mouth	Posterior pharyngeal wall

According to the 8th edition of the Union for International Cancer Control (UICC) tumor node metastasis (TNM) classification

Quality of life, local control, and OS 12 months after RT are the secondary endpoints of the trial. After 12 months of study specific follow-up, the patients will continue with regular clinical follow-up examinations. Also, patient-reported outcomes (PRO) and dental status, as well as plan comparisons and robustness analyzes, will be assessed as exploratory endpoints. Also, the functional and differentiation parameters, as well as the regenerative and radioprotective factors of gingival MSCs will be evaluated in vitro.

